**Fig. 3 Fig3:**
[figure not shown]
Visual representation of activities occurring during the MEGA-MAC study. Abbreviations: MAC, medication advisory committee; MEGA-MAC, national quality improvement collaborative

Ongoing fidelity of the intervention delivered by the knowledge broker dyads will be monitored using the local action plans, the MEGA-MAC meetings and regular meetings with the Project Management Team.

### Data collection

Data will be collected from the participating RACFs at six timepoints (−6, −3, baseline, 3, 6, 9 months) by trained data collectors (aged care nurses, health or care professionals employed or contracted by each of the participating aged care provider organisations) (Table 2). Data collectors will attend an online training webinar on data collection led by the Project Management Team and will have access to data collection manuals and recorded training webinars to ensure consistency of data collection. Pre-intervention data (−6, −3, 0 months) will be collected retrospectively at or before baseline. Post-intervention data (+ 3, + 6, and + 9) will be collected prospectively. Trial data will be collected using a series of standard data collection forms and managed using Research Electronic Data Capture (REDCap), an electronic data capture tool hosted and managed by Helix (Monash University). REDCap is a secure, web-based software platform designed to support data capture for research studies [36, 37]. Trial data will be stored for a minimum of 15 years after publication of result in accordance with Australian National Health and Medical Research council (NHMRC) and Monash University guidance for medical research involving clinical trials. The final dataset will only be accessible to the investigators and statistician or epidemiologist.

**Table 2 Tab2:** SPIRIT diagram – schedule of enrolment, intervention and assessment for the MEGA-MAC study

	Study period							Data source
Timepoint (months)	Pre-intervention period		Enrolment	Baseline	Intervention period			
	−6	−3	*-t*	0	3	6	9	
RACF enrolment								
Eligibility screen			x					
Consent			x					
Intervention								
KB dyad recruitment			x					
MEGA-MAC collaborative panel recruitment			x					
KB training			x					
Intervention implementation				x	x	x	x	
Data collection								
RACF characteristics information				x				Clinical and administration records; knowledge broker dyads
MAC characteristics information				x			x	Clinical and administration records; knowledge broker dyads
KB dyad and MEGA-MAC collaborative panel demographic information			x					Knowledge brokers and MEGA-MAC members
RACF concordance with Guiding Principles	x	x		x	x	x	x	NQIP records; psychotropic medicines register; nursing progress notes; medical records; RACFs register of policies/procedures/guidelines; register of residents who have CMR by a pharmacist; register of resident admitted to the RACF; MAC meeting agenda/minutes/associated papers
RACF-level proportions of hospitalisations, resident QoL, consumer experience, medication incidents	x	x		x	x	x	x	NQIP records, RACF electronic risk management system
Knowledge broker dyad activities				x	x	x	x	Local action plans; semi-structured interviews, online MEGA-MAC meeting surveys
Economic evaluation – intervention costs							x	MEGA-MAC project budget; MEGA-MAC meeting agenda/minutes/associated papers
Economic evaluation – downstream costs for the RACF				x			x	RACF staff
Economic evaluation – downstream costs for the RACF’s MAC	x	x		x	x	x	x	MAC meeting agenda/minutes/associated papers; MAC members

*CMR* comprehensive medication review, *KB* knowledge broker, *MAC* Medication Advisory Committee, *MEGA-MAC collaborative* national quality improvement collaborative, *NQIP* National Aged Care Mandatory Quality Indicator Program, *RACF* residential aged care facility, *-t* prior to baseline, *QoL* quality of life

### RACF-level concordance with Guiding Principles

The data collectors will assess RACF-level concordance with the Guideline Principles using a series of indicators developed for the MEGA-MAC trial by New South Wales Therapeutic Advisory Group (NSW TAG), in consultation with an expert advisory group and the Project Management Team [38]. The indicators will assess concordance with the Guiding Principles across four key domains: the RACF’s 1) MAC meeting; 2) policies, procedures and guidelines; 3) admission processes; and, 4) medication review processes (Tables 3, 4, 5, and 6). There will be 28 indicators across the four domains.

**Table 3 Tab3:** Domain 1 Indicators and sub-indicators evaluating the RACF’s MAC meeting

Indicator	Numerator	Denominator	Target
Calculation of summary indicator			
Percentage of recommended medication governance activities undertaken by the RACF	Number of positive or NA responses to the listed RACF’s medication governance and management activities	9 (total number of responses)	High (towards 100%)
Sub-indicators regarding aspects of MAC structure or function		Possible responses	
1. The RACF’s MAC met in the last quarter		Yes/No	
2. The RACF’s MAC meeting was multidisciplinary		Yes/No	
3. When a MAC governs more than one RACF, a representative of this RACF was in attendance		Yes/No/NA*	
4. The RACF’s report of residents’ experiences from RACF residents, their carers, family and/or substitute decision-makers regarding medication-related issues was presented		Yes/No	
5. The RACF’s report of RACF storage of medicines was presented		Yes/No	
6. The RACF’s report of medication incidents was presented		Yes/No	
7. The RACF ‘s report of trends in the percentage (or numbers) of residents with polypharmacy was presented		Yes/No	
8. The RACF’s report of trends in the percentage (or numbers) of residents who received an antipsychotic medication was presented		Yes/No	
9. The RACF’s report of trends in the percentage (or numbers) of residents who received a comprehensive medication management review from an appropriately qualified pharmacist was presented		Yes/No	

^*^ NA is selected if the MAC governs one RACF only. One point is allocated for selecting N/A in response to this indicator

*MAC* medication advisory committee, *NA* not applicable, *RACF* residential aged care facility

**Table 4 Tab4:** Domain 2 Indicators and sub-indicators evaluating the RACF’s policies, procedures and guidelines

Indicator	Numerator	Denominator	Target
Calculation of summary indicator			
Percentage of recommended and current RACF policies, procedures and guidelines	Number of recommended and current RACF’s documents supporting medication management processes/activities	10 (total number of statements)	High (towards 100%)
Sub-indicators regarding recommended and current RACF’s policies, procedures and/or guidelines		Possible responses	
1. The collection and review of feedback from the resident, carers, family and/or substitute decision-makers regarding medicine use		Available: Yes/No Current: Yes/No/NA*	
2. The provision of written medicines-related information to the resident, their carers, family and/or substitute decision-makers as part of any clinical consultation		Available: Yes/No Current: Yes/No/NA*	
3. The residents’ use of complementary and self-selected non-prescription medicines		Available: Yes/No Current: Yes/No/NA*	
4. A list of approved non-prescription nurse-initiated medications		Available: Yes/No Current: Yes/No/NA*	
5. The documentation of medication incidents and management of potential or actual harm arising from the medication incidents		Available: Yes/No Current: Yes/No/NA*	
6. Obtaining a best possible medication history (BPMH)		Available: Yes/No Current: Yes/No/NA*	
7. The roles and responsibilities of healthcare professionals regarding the use and review of medication chart		Available: Yes/No Current: Yes/No/NA*	
8. The continuity of medicines supply for all residents receiving care		Available: Yes/No Current: Yes/No/NA*	
9. The appropriate storage of all medications requiring refrigeration		Available: Yes/No Current: Yes/No/NA*	
10. The appropriate storage of all Schedule Eight (S8) medications		Available: Yes/No Current: Yes/No/NA*	

^*^NA is selected if the RACF does not have the recommended policy, procedure or guideline available. A score of zero is allocated for a NA response

*BPMH* best possible medication history, *NA* not applicable, *RACF* residential aged care facility, *S8* schedule eight medication

**Table 5 Tab5:** Domain 3 Indicators and sub-indicators evaluating the RACF’s admission process

Indicators	Numerator	Denominator	Target
Calculation of summary indicator			
Percentage of newly admitted residents who have received recommended medicine-related admission processes	Number of residents admitted within the last 3 months with recommended medicine-related admission processes	Number of residents admitted within the last 3 months	High (towards 100%)
Sub-indicators for activities or processes documented at admission			
1. Percentage of newly admitted residents who have their medicine needs, preferences and medicine-taking behaviours documented	Number of residents admitted within the last three months who have their medicine needs, preferences and medicine-taking behaviours documented at admission	Number of residents admitted within the last 3 months	High (towards 100%)
2. Percentage of newly admitted residents wishing to self-administer medicines who were assessed for their capability to self-administer medications	Number of residents admitted within the last 3 months wishing to self-administer any of their medications who have their ability to self-administer these medication(s) assessed	Number of residents admitted within the last 3 months who wish to self-administer any of their medications	High (towards 100%)
3. Percentage of newly admitted residents with swallowing difficulties whose oral medications within their medication regimen have been assessed for appropriateness	Number of residents admitted within the last 3 months with swallowing difficulties who have the oral medications within their medication egimens assessed for appropriateness	Number of residents admitted within the last 3 months with swallowing difficulties	High (towards 100%)
4. Percentage of newly admitted residents with their vaccination status documented	Number of residents admitted within the last 3 months who had their vaccination status for influenza and COVID-19 documented	Number of residents admitted within the last 3 months	High (towards 100%)
5. Percentage of newly admitted residents who have nominated a person responsible for medicines-related decisions	Number of residents admitted within the last 3 months who have a nominated person responsible for medicines-related decisions documented	Number of residents admitted within the last 3 months	High (towards 100%)

*RACF* residential aged care facility

**Table 6 Tab6:** Domain 4 Indicators evaluating the RACF’s medication review processes

Indicators	Numerator	Denominator	Target
Calculation of primary indicator			
1.Percentage of residents who have received a CMR by an appropriately qualified pharmacist within the last year	Number of residents who have received a CMR by an appropriately qualified pharmacist within the last 12 months	All current non-respite RACF residents	High (towards 100%)
Calculation of secondary indicators			
2. Percentage of newly admitted residents who have received a CMR by an appropriately qualified pharmacist since their RACF admission	Number of RACF residents admitted within the last 3 months who have received a CMR by an appropriately qualified pharmacist since their RACF admission	All newly admitted non-respite RACF residents	High (towards 100%)
3. Percentage of residents with polypharmacy who have received a CMR by an appropriately qualified pharmacist within the last year	Number of residents prescribed nine or more medications as per NQIP audit and who have received a CMR by an appropriately qualified pharmacist within the last 12 months	All non-respite RACF residents with polypharmacy	High (towards 100%)
4. Percentage of residents receiving an antipsychotic medication who have received a CMR by an appropriately qualified pharmacist within the last year	Number of residents who received an antipsychotic medication as per NQIP audit and have received a CMR by an appropriately qualified pharmacist within the last 12 months	All non-respite RACF residents receiving an antipsychotic	High (towards 100%)

*CMR* comprehensive medication review, *NQIP* national quality indicator program, *RACF* residential aged care facility

Data required for the indicators will be extracted from the RACF’s existing clinical information systems, including National Aged Care Mandatory Quality Indicator Program records, psychotropic medicines register, nursing progress notes, medical records, RACFs register of policies/procedures/guidelines, register of residents who have a completed comprehensive medication management review by a pharmacist, register of residents admitted to the RACF and MAC meeting agenda, minutes, and associated papers. The identifiable resident-level data required to complete the indicators will only be accessed by appropriate staff employed/contracted by the aged care provider organisation and by the knowledge broker dyad to assist with intervention delivery. Trial investigators will not have access to these data sources. Microsoft Excel-based ‘Guiding Principles Concordance’ data collection tools [38] were developed for the trial to assist data collectors in calculating RACF-level concordance for each trial indicator and sub-indicator. RACF-level concordance will be entered into REDCap. Aggregated data on Guiding Principles concordance for all participating RACFs will be reported at quarterly MEGA-MAC meetings and in the MEGA-MAC newsletters.

### RACF-level proportions of hospitalisation, quality of life, consumer experience, and medication-related incidents

Data on RACF-level proportions of hospitalisation, quality of life, and consumer experience will be extracted from the mandatory National Aged Care Quality Indicator Program records [39]. The following definitions will be used in line with the National Aged Care Quality Indicator Program:Hospitalisation: RACF-level proportion of residents hospitalised compared to the previous quarter. Hospitalisation will include emergency department presentations and hospital admissions within the last 3 months.Quality of life: RACF-level proportion of residents who report ‘excellent’ or ‘good’ quality of life as assessed using The Quality of Life Aged Care Consumers (QOL-ACC) tool compared to the previous quarter [40].Consumer experience: RACF-level proportion of residents who report ‘excellent’, or ‘good’ consumer experience using The Quality of Care Experience Aged Care Consumers (QCE-ACC) compared to the previous quarter.

Data on RACF-level prevalence of medication-related incidents will be extracted from each RACF’s electronic risk management system quarterly.

### RACF and MAC characteristics

Data on RACF-level characteristics will include: location (e.g. State, Territory), region (e.g. metropolitan, regional, rural, remote), number of residents, number of beds, number of residents who are female, mean resident age, number of health and care professionals employed/contracted and the health professional disciplines that typically visit the RACF weekly. Data on MAC characteristics will include: number of RACFs and residents the MAC governs, number of MAC members, discipline of each MAC member (e.g. general practitioner, nurse, pharmacist) and the discipline of the MAC chair. RACF characteristics will be collected at baseline. MAC characteristics will be collected at baseline and 9 months.

### Knowledge broker and MEGA-MAC Collaborative demographics

Demographic data will be collected from each knowledge broker dyad and MEGA-MAC collaborative panel member at time of recruitment. Knowledge broker demographics will include: gender, discipline (e.g. general practitioner, registered nurse, pharmacist), professional background (education, qualifications, practice experience, aged care experience) and length of time employed or contracted at the RACF. MEGA-MAC collaborative panel member demographics will include: gender, discipline (e.g. general practitioner, registered nurse, pharmacist), professional background (education, qualifications, practice experience, aged care experience, current role/s) and consumer roles.

### Knowledge broker dyad activities

Data from local action plans (including goals, type of local activities implemented, resources used, timeline, actual implementation, reflections) and MEGA-MAC meetings will be collected throughout the trial. Semi-structured interviews with knowledge broker dyads will also be conducted at 3 months, 6 months and at the conclusion of the trial to understand the delivery of the intervention at each RACF. Semi-structured interviews may also be conducted with other stakeholders at the conclusion of the trial. Optional anonymous online surveys will be conducted at the conclusion of each MEGA-MAC meeting to understand attendees’ perspectives on the meeting (e.g. aspects of the meeting that were useful, aspects that could be improved).

### Economic evaluation

Data for economic evaluation will include interventions costs (e.g. how much the intervention costs to be delivered), downstream costs (e.g. staff costs to attend MAC meetings), and costs of medication incidents and hospitalisations. Individual resident level data will not be collected, only RACF-level data. Economic data will be embedded within other trial data collection tools to minimise data collection burden where possible (refer to Appendix 2 for full details).

## Outcomes

### Primary outcome

The primary outcome will be the change in RACF-level concordance with the Guiding Principles post-intervention compared to pre-intervention. Concordance with the Guiding Principles will be measured as a score out of 28. This score will be composed of 19 indicators measured dichotomously (no = 0, yes = 1) and 9 indicators measured continuously (proportion between 0 and 1) (Tables 3, 4, 5 and 6). Higher scores will indicate greater concordance with the Guiding Principles.

### Secondary outcomes

Secondary outcomes will include change in the following outcomes post-intervention compared to pre-intervention:RACF-level concordance with trial indicators in each of the four key domains: 1) MAC meeting (Table 3); 2) policies, procedures and guidelines (Table 4); 3) admission processes (Table 5); and 4) medication review processes (Table 6).RACF-level concordance with each of the 28 individual sub-indicatorsRACF-level proportion of residents with one or more emergency department presentations or hospital admission. Proportion will be calculated using the total number of care recipients assessed for hospitalisation as a denominator.RACF-level proportion of residents who report ‘excellent’ or ‘good’ quality of life. Proportion will be calculated using the total number of care recipients who completed the quality of life assessment as a denominator.RACF-level proportion of residents who report ‘excellent’ or ‘good’ consumer experience. Proportion will be calculated using the total number of care recipients who completed the consumer experience assessment as a denominator.RACF-level total number of medication incidents reported in the previous three months.

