### Economic analysis

A net benefit analysis will be conducted to examine the relative costs and benefits of implementing the intervention. We will model the results of the economic evaluation over several perspectives, including the perspective of the RACF, the Australian government as the funder of health and aged care and from a societal perspective. With each of these perspectives, we will vary the assumptions of who would be the payer of the program, with one set of models looking at if the RACFs was paying for the program directly, and another where the government would pay.

Modelling of cost data is required in this evaluation and economic assumptions will be made. Costs will include the direct costs of the intervention (e.g. salary costs of the knowledge broker) and downstream costs (e.g. staff time preparing for MAC meetings). Benefits will consider the monetised impact of hospitalisations and medication incidents. Measurement and valuation of activity will either be collected internally from the trial budget (e.g. salary costs of the knowledge broker) or valued using market rates (e.g. national or state-based awards as relevant) or by extrapolation based on previously published work for costs from external sources (e.g. the cost of staff to attend a MAC). The mean (Standard Deviation) will be presented for the cost of the intervention, downstream costs, cost of medication incidents and hospitalisations. To overcome variability in resident numbers at each of the RACFs included in the trial, the cost of the intervention, downstream costs, and costs of medication incidents and hospitalisations will be presented per bed at the RACF. Cost data will be presented in Australian dollars (AUD). Costs will be inflated accordingly by consumer price index (CPI) and presented as a consistent base year (e.g. 2025/2026 financial year).

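### Medication incidents carry three different units, and the outcome list uses a raw total with no denominator, so a change in resident numbers can look like an intervention effect

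*Protocol article*

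**What the plan says.** The protocol article describes medication incidents in four places.

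- **Secondary outcomes:** "RACF-level total number of medication incidents reported in the previous three months". This is a count of events, with no denominator.
- **Table 2 (schedule of assessments):** the row reads "RACF-level proportions of hospitalisations, resident QoL, consumer experience, medication incidents" and is marked at all six time points.
- **Data-collection heading:** "RACF-level proportions of hospitalisation, quality of life, consumer experience, and medication-related incidents".
- **Text under that heading:** "Data on RACF-level prevalence of medication-related incidents will be extracted from each RACF"; the source is the facility's electronic risk management system, read quarterly.

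The neighbouring outcomes are treated differently. For hospitalisation, the Secondary outcomes section says: "Proportion will be calculated using the total number of care recipients assessed for hospitalisation as a denominator". Quality of life and consumer experience each have a stated denominator too.

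The Economic analysis section presents costs, including the cost of medication incidents, per bed. The reason given is "To overcome variability in resident numbers at each of the RACFs included in the trial".

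**The concern.** There are two problems, and the second depends partly on the first.

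**The quantity is not fixed.** A proportion or prevalence of incidents normally means the share of residents with at least one incident. A total counts events, and one resident can have several. The two need different extractions from the incident system. The Economic evaluation part of the data-collection section says that only facility-level data are collected, so a recorded total cannot later be turned into a share of residents. Data collectors at three provider organisations could reasonably read the sections differently.

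**The listed definition depends on how many residents are in care.** Secondary outcomes are analysed as change from before to after the intervention, with no concurrent control group. If resident numbers change between the periods, the total changes with them, and nothing in the stated definition separates that from a change in medication safety. The economic section shows that the authors regard resident numbers as worth scaling for; the effectiveness outcome is not scaled.

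**Working it through.** The protocol gives no numerical figure for this outcome, so there is none to reproduce. The check has four steps.

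**1. Do the three labels differ?** Take 80 residents and 12 incidents in a quarter (illustrative figures).

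- Total = 12.
- If 12 residents had one incident each, the proportion affected is 12/80 = 15%.
- If 3 residents had four each, it is 3/80 = 3.75%.

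The total is the same and the proportion differs fourfold, so the labels are not interchangeable.

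**2. What does a change in resident numbers do to the total?** Expected count = rate per resident × number of residents. With the rate constant:

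- occupancy 85% to 95% (assumed): 0.95/0.85 − 1 = +11.8%
- occupancy 95% to 85% (assumed): 0.85/0.95 − 1 = −10.5%

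At an assumed 0.15 incidents per resident-quarter, a facility with 80 residents expects 0.15 × 80 = 12.0 incidents. That becomes 12.6 with 5% more residents, 13.2 with 10% more and 10.8 with 10% fewer. The rate stays at 0.15 throughout.

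**3. Does this reach the trial's estimate?** A simulation with no true effect was run, 400 runs per setting.

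- Assumptions: 15 facilities of 30 to 149 residents, six time points, Poisson counts at 0.15 per resident-quarter. Resident numbers step by the same percentage in every facility when the intervention starts.
- Model: period, trial month and facility. Facility was a fixed effect, as a within-facility analogue of the mixed model that the protocol states for the primary outcome.

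| Step in resident numbers | Raw total: mean period estimate (incidents) | Raw total: rejection at nominal 5% | Per 100 residents: mean period estimate | Per 100 residents: rejection |
|---|---|---|---|---|
| 0% | −0.18 | 5.8% | −0.14 | 2.8% |
| −5% | −0.70 | 8.3% | +0.11 | 4.0% |
| +5% | +0.60 | 7.0% | +0.09 | 6.5% |
| +10% | +1.29 | 12.5% | +0.02 | 3.5% |
| +20% | +2.76 | 32.5% | +0.13 | 5.5% |

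The simulation standard error of a 5% rejection rate is √(0.05 × 0.95/400) = 1.1 percentage points. The mean size is 89.5 residents, so the mean count is 0.15 × 89.5 = 13.4. A 10% step should therefore shift the estimate by about 1.3 incidents and a 20% step by about 2.7, which agrees with the table. The first row shows that very unequal but stable sizes create no false effect.

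**4. Weighting.** Apply the same 10% relative change to two facilities at the assumed rate. With 120 residents the count moves from 18.0 to 19.8, a change of 1.8. With 40 residents it moves from 6.0 to 6.6, a change of 0.6. On the absolute scale the larger facility contributes three times as much. This concerns what the average represents; it is not bias.

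**The case against.** The best defence has five parts.

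- **Facility size cancels.** A reader might infer that the spread of sites, from metropolitan to remote and with no size limit, itself distorts the result. It does not. Each facility is compared with itself, and the 0% row above shows no false effect. Only the weighting point remains.
- **No occupancy shift is documented.** This stands. To mimic an effect, resident numbers would have to move in the same direction across facilities at about the time the intervention starts. A 5% step does little, and a trial-month term, if used for this outcome too, would take up part of a gradual drift. The harm is something that can happen, not something shown to happen.
- **An offset may be in the statistical analysis plan.** It may, and the absence of a model for this outcome from the article is not the complaint. But an analysis plan would not remove the contradiction in the protocol, and it could not recover a quantity that was never extracted.
- **A usable denominator exists.** Because the section on facility and committee characteristics says "RACF characteristics will be collected at baseline", a reader might infer that any quarterly rate would rest on an out-of-date resident count. The documents do not support that: the hospitalisation outcome uses a care-recipient count and is scheduled at all six time points. What they leave open is whether that count, or only the resulting proportion, is entered in the trial data.
- **The economic analysis already scales.** A reader might infer that the net benefit result is wrong as well. Incident costs are presented per bed, and no error in that analysis is shown.

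**Conclusion.** The point holds in a limited form. The inconsistency is plain on the page: one secondary outcome is named as a proportion, a prevalence and a total, and the version in the outcome list alone lacks a denominator among the resident-related outcomes. In an uncontrolled pre/post series, that version lets a change in resident numbers appear as an intervention effect.

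The size depends on assumptions that the protocol cannot settle. A uniform step of 10% or 20% at intervention start raised false-positive rates to 12.5% and 32.5%; a 5% step gave 7% to 8%. These rates rest on the assumed 0.15 incidents per resident-quarter, and a higher incident rate would make the same percentage shift easier to detect as a false effect. A per-resident rate stayed at about 3% to 7% in every setting.

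The consequence is confined to this secondary outcome. It is worth correcting because the remedy is cheap and the extraction must be settled in any case.

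**What to change.** Use one definition in Table 2, in the data-collection section (heading and text) and under Secondary outcomes: medication incidents per 100 care recipients in the quarter, or per 1,000 occupied bed-days. State that events are counted, so that one resident may contribute several, and drop the words proportion and prevalence for this outcome.

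Analyse the count with the chosen denominator as an offset, so that the effect is a change in rate. This also stops the largest facilities from dominating an absolute change.

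For the denominator, use the quarterly care-recipient count behind the hospitalisation proportion and record it in the trial data at all six time points. Incidents come from a different system, so confirm that both cover the same residents.

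The cost is a wording change in three places. If only the hospitalisation proportion is currently entered, one extra number per facility per quarter is needed as well; if bed-days are preferred, they must be collected each quarter.
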